### Study intervention

All study drugs and dosages are routinely used in clinical practice and will be ordered/dispensed as per each site’s institutional practice from the hospital pharmacy. The active control arm will receive IV ceftriaxone 2 g or ertapenem 1 g daily (adjusted for renal function) started immediately post randomization, and continued for four weeks from the date of randomization which is the standard dose used in clinical practice for complicated intra-abdominal infections including liver abscess. The intervention arm will receive oral ciprofloxacin 750 mg or trimethoprim/sulfamethoxazole 5 mg/kg twice daily (adjusted for renal function) started immediately post randomization, and continued for at least four weeks from the date of randomization. These antibiotics have been selected due to their prior extensive use in clinical practice with well-established safety and efficacy across a wide range of infections. They are also available as affordable generics. Ciprofloxacin is approximately 70% bioavailable. A 750 mg oral dose given every 12 hours has been shown to produce an area under concentration-time curve (AUC) at steady-state equivalent to that produced by an IV infusion of 400 mg given over 60 minutes every eight hours. A 750 mg oral dose results in a maximum measured plasma concentration (C_max_) similar to that observed with a 400 mg IV dose [18]. Trimethoprim/sulfamethoxazole is rapidly absorbed following oral administration. Peak blood levels for the individual components occur one to four hours after oral administration. During administration of 800 mg sulfamethoxazole and 160 mg trimethoprim twice a day, the mean steady-state plasma concentration of trimethoprim was 1.72 μg/mL which is well above the minimum inhibitory concentration (MIC) for susceptible Enterobacteriaceae including *K. pneumoniae*[19].

Ceftriaxone and ertapenem will be given IV using either peripheral cannula or a peripherally inserted central catheter (PICC) once daily. Administration may be done as inpatient, in OPAT or a step-down facility by healthcare staff, or at home by patients or their caregivers after training by OPAT staff (all these methods are currently in routine clinical use for patients on prolonged IV antibiotics). Ciprofloxacin and trimethoprim/sulfamethoxazole will be administered orally in tablets from each site’s pharmacy either as inpatient or at home. Patients on ciprofloxacin may not take tizanidine or theophylline or concomitant drugs that can result in prolongation of the QT interval (for example, class IA or class III antiarrhythmics).

### Safety considerations

'Unanticipated Problems Involving Risk to Subjects or Others’ (UPIRTSO) events and serious adverse events will be reviewed and classified by the site principal investigator (PI) or other investigator. Severity will be classified using a standard set of criteria for grading adverse events (Common Terminology Criteria for Adverse Events version 4.03). The relationship of the event to the study drug, and whether the event is an expected event or not, will be assessed using the listing of adverse effects contained in the summary of product characteristics for the antibiotics used. All SAEs that are unexpected and related to the study drug will be reported to the Health Science Authority (HSA).

A Data Safety Monitoring Board (DSMB) will be established, comprising two independent physicians and a statistician. An interim analysis - including both efficacy and safety endpoints will be performed after the first 50 subjects have completed 12 weeks of the study. The trial statistician will provide details of safety outcomes and any significant differences in efficacy according to treatment arm to the DSMB. These will be highlighted to the Trial Steering Committee along with the DSMB’s recommendations for action. If there is a significant safety concern raised by the, the DSMB may recommend to the PI that the trial should be stopped.

As stated in the Participant Information Sheet, complaints may be made to each site PI or the Domain Specific Review Board (DSRB). Complaints will be handled according to the normal procedures in operation in NUH, TTSH and SGH.

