### Study endpoints

The primary endpoint is 'clinical cure’, determined at Week 12 post-randomization, and defined as CRP < 20 mg/l, plus absence of documented fever ≥ 38°C in the preceding week, plus most recent abdominal imaging showing that the maximal diameter of the abscess has reduced.

The main secondary endpoint is 'clinical response’, determined at Week 4 post-randomization, and defined as CRP < 20 mg/l, plus absence of documented fever ≥ 38°C in the preceding week, plus most recent abdominal imaging showing that the maximal diameter of the abscess has reduced. Other secondary endpoints (assessed at Week 12) are:

• all-cause mortality at any point between randomization and Week 12;

• unplanned readmission for any cause at any point between hospital discharge and Week 12;

• unplanned need for drainage after enrollment at any point between randomization and Week 12 (the screening visit will document any plans for elective drainage);

• metastatic complications occurring at any point between randomization and Week 12;

• new *K. pneumoniae* bacteremia occurring at any point between the first negative blood culture, and Week 12, with the same strain of *K. pneumoniae* as the original blood culture or abscess fluid culture determined by antibiotic susceptibility pattern);

• length of hospital stay (from the date of randomization to the end of inpatient stay, censored at Week 12);

• length of time the subject requires medical leave following hospital discharge (censored at Week 12);

• subject quality of life as defined by the WHOQOL-BREF assessed at Week 4 and Week 12 post-randomization;

• overall cost of each treatment strategy from the payer and total societal perspective for the course of the study until the final 12 Week follow-up;

• level of adherence during the entire study period, assessed at 12 weeks. Subject deemed to be compliant if 80% or more of prescribed antibiotics have been taken.

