Safety endpoints include: need to stop study drug due to toxicity; toxicity as defined by Common Terminology Criteria for Adverse Events version 4.03 [17]; all adverse events (occurrence of adverse events up to 12 weeks post randomization or 30 days post last study dose if later than 12 week visit); serious adverse events (occurrence of serious adverse events at any time during the study period, whether or not they are thought to be related to the study drugs); need to escalate antibiotics due to worsening infection or secondary infection at any point between randomization and Week 12; vascular catheter complications at any point between randomization and Week 12.

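### The DSMB receives by-arm efficacy only when a difference is significant, so at 50 patients a large cure deficit on oral therapy would often not be shown to it

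*Protocol article*

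**What the plan says.** Under Safety considerations, the protocol article sets up a three-member DSMB and describes one interim analysis. Its content is broad: "An interim analysis - including both efficacy and safety endpoints". Its timing is also fixed: it "will be performed after the first 50 subjects have completed 12 weeks of the study". The reporting rule that follows is asymmetric: "The trial statistician will provide details of safety outcomes and any significant differences in efficacy according to treatment arm to the DSMB". Neither a test nor a significance level is attached to that condition.

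Under Study endpoints, the primary endpoint is clinical cure at Week 12 and the main secondary endpoint is clinical response at Week 4. Both use the same CRP, fever and imaging criteria. The section on sample size calls the primary endpoint an efficacy endpoint.

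A further list opens with "Other secondary endpoints (assessed at Week 12) are". It contains all-cause mortality, unplanned readmission, unplanned drainage, new *K. pneumoniae* bacteremia and "metastatic complications occurring at any point between randomization and Week 12".

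The safety endpoints are a separate list. It includes "need to stop study drug due to toxicity", all adverse events, escalation of antibiotics for worsening or secondary infection, and catheter complications. It also takes in every serious event, whatever its link with treatment: "serious adverse events (occurrence of serious adverse events at any time during the study period, whether or not they are thought to be related".

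**The concern.** The experimental strategy replaces four weeks of IV treatment with oral treatment after at most a week of effective IV therapy. Its main risk is loss of efficacy, and cure and Week 4 response measure that directly. Those are the results that the rule withholds unless they are significant, although the interim analysis will already have computed them.

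A significance test with about 25 patients per arm is a weak gate. In a non-inferiority trial, a non-significant difference at that size says almost nothing about whether the deficit is below 12 points. A board that receives no efficacy table cannot distinguish equal arms from a deficit that is large but not significant.

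Only one interim look is described. With even accrual (an assumption), 152 patients over 24 months is 6.33 per month. The 50th patient enrols at 50/6.33 = 7.9 months and reaches Week 12 about 2.8 months later, at month 10.7. By then 10.7 × 6.33 gives about 67 patients enrolled. The advice therefore bears on the remaining 85 or so.

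**Working it through.** The protocol gives no figure for the reporting rule, so there is none to reproduce. The check asks what the rule would let through.

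**Inputs from the protocol article**
- 50 patients at the interim (Safety considerations) and 1:1 allocation (Randomization), so about 25 per arm.
- Assumed control cure 95% and margin 12 points (Determination of sample size).
- Fisher's exact test, which Statistical analysis names for binary endpoints other than the primary.

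**Assumptions, because the protocol does not state them**
- Significant means a two-sided Fisher p below 0.05, applied to cure as well.
- The split is 25/25, with 24/26 and 26/24 (oral/IV) also checked.

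**Step 1: one concrete result.** Cure in 19/25 oral and 24/25 IV patients means 6 versus 1 failures, 76% versus 96%, a 20-point deficit. With 7 failures among 50:
- P(6 oral, 1 IV) = C(25,6)·C(25,1)/C(50,7) = 4,427,500/99,884,400 = 0.0443
- P(7 oral, 0 IV) = C(25,7)/C(50,7) = 480,700/99,884,400 = 0.0048
- One tail = 0.0491. The arms are equal in size, so two-sided p = 2 × 0.0491 = 0.098.

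This result is not sent. With one IV failure, 7 oral failures are needed (p = 0.049). Cure in 16/25 versus 22/25, a 24-point deficit, gives p = 0.095 and is not sent either.

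**Step 2: how far single results depend on the unstated details.** The same 6 versus 1 failures with 24 oral and 26 IV patients give Fisher p = 0.045 and would be sent. With 26 oral and 24 IV, p = 0.100. An uncorrected chi-square at 25/25 has z = 0.20/√(0.14 × 0.86 × 2/25) = 0.20/0.0981 = 2.04, p = 0.042, and would be sent. The missing test and level can therefore decide what the board sees.

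**Step 3: chance that a true deficit is flagged.** This sums over all outcomes:

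P(flag) = Σ Bin(a; n_oral, p_oral) × Bin(b; n_IV, p_IV), over pairs (a, b) with Fisher p < 0.05 and oral cure lower.

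| True cure, IV v oral | 25/25 | 24 oral/26 IV | 26 oral/24 IV |
|---|---|---|---|
| 95% v 83% (deficit equal to the margin) | 11% | 25% | 11% |
| 95% v 75% | 37% | 51% | 35% |
| 95% v 70% | 55% | 66% | 54% |

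At these splits, a true deficit equal to the margin goes unreported at least about three times in four. A 20-point deficit goes unreported in roughly half to two thirds of trials.

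**Step 4: does safety reporting close the gap?**
- *Cure and Week 4 response:* no. Neither is in the safety list. A CRP of 20 mg/l or more, or an abscess that has not shrunk, is not necessarily an adverse event.
- *Death, metastatic complications, bacteremia, drainage, readmission:* largely, for individual events, through the adverse event and serious adverse event listings. But the text does not say which side of the filter these endpoints fall on, so by-arm counts under their protocol definitions are not assured.
- *Escalation of antibiotics:* yes. It is a named safety endpoint and already unfiltered.

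**The case against.** A reader might infer something stronger: that the infectious harms of early step-down are classed as efficacy and hidden from the board, so that even 5 versus 0 metastatic infections would go unreported. The documents do not support this, for three reasons.

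- The list containing these events is headed as other secondary endpoints, not efficacy. Secondary status does not imply efficacy: the Objectives section puts antibiotic escalation and catheter complications in the same secondary group, and Study endpoints then treats both as safety.
- Safety outcomes go to the board unfiltered. They include all adverse events and all serious adverse events whatever their relation to study drug, and Statistical analysis tabulates both by treatment group. New metastatic infections would ordinarily appear there.
- The 5 versus 0 example turns on one patient. Fisher p is 0.0502 at 25/25 but 0.020 with 24 oral and 26 IV patients.

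Two further objections are fair. The layout of a closed report is often left to a DSMB charter, which an article need not reproduce. And the Fisher test and the 0.05 level at the interim are assumptions.

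The first would answer a silent protocol, but this one states a rule, and a charter written to match it would carry the filter forward. The second limits how much weight any single example can bear, including 19/25 versus 24/25. It does not rescue the rule: flagging stays unlikely for a deficit equal to the margin at every split checked, and a stricter level would make it less likely.

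**Conclusion.** The point holds in a limited form. As written, by-arm cure and Week 4 response reach the DSMB only if significant, by an unspecified test at an unspecified level. With about 25 per arm and two-sided Fisher at 0.05, the rule would pass on a true deficit equal to the 12-point margin about 11% of the time (11–25% across the splits checked), a 20-point deficit 37% (35–51%) and a 25-point deficit 55% (54–66%). These figures assume 95% cure on IV treatment.

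For death, metastatic complications, new bacteremia, unplanned drainage and readmission, the gap is one of presentation. The events should ordinarily be visible as adverse events, but their by-arm reporting as defined endpoints is not assured. This is a cheap improvement to the board's report. It does not show that the trial leaves its patients without safety oversight.

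**What to change.** Under Safety considerations, remove significance as a condition for sending efficacy results. State instead that the closed DSMB report always gives by-arm counts with 95% intervals, whatever the p-value, for:
- Week 12 cure and Week 4 response;
- death, metastatic complications, new bacteremia, unplanned drainage and readmission.

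Antibiotic escalation stays where it is, as an unfiltered safety endpoint. The DSMB charter should carry the same list. Adding Week 4 response for patients enrolled after the first 50 is optional.

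The cost is a sentence or two in the protocol and charter and a fuller closed report from data already collected. No treatment rule, sample size or final analysis changes. The small downside is that the board must interpret small numbers without a p-value gate, which the intervals help it to do.

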### Study design

This study is a multi-center randomized open-label active comparator-controlled non-inferiority trial. Subjects fulfilling the inclusion/exclusion criteria are randomized to one of two arms: intervention arm; or active control arm, as shown in Figure 1. Participants randomized to the active control arm will receive IV ceftriaxone 2 grams daily (or ertapenem 1 gram daily if resistant) to complete a total of four weeks of IV antibiotics until the assessment at Week 4 post randomization. Patients can be discharged to OPAT at any point post randomization if clinically well, at the discretion of the treating physician/ID team. Patients discharged to step-down care will be followed up in OPAT clinic at the same weekly intervals as patients discharged to home. Patients will be assessed at Week 4 for clinical response. If they do not meet criteria for clinical response (as defined in the section on endpoints) then they will receive a further two weeks of oral ciprofloxacin 750 mg twice daily (or trimethoprim/sulfamethoxazole 5 mg/kg twice daily if resistant) and then re-reviewed (see below).

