### Randomization

After informed consent is signed, randomization into intervention or active control arms will be performed with a 1:1 allocation ratio. Balanced treatment assignments will be achieved using permuted block randomization, stratified by:

1) Abscess drainage (yes/no);

2) *K. pneumoniae* resistant to first-line agents (ceftriaxone or ciprofloxacin) (yes/no);

3) Study site.

The block length is determined by the study statistician and will not be made known to the clinical investigators or site personnel. All randomization will go through SCRI. Randomization will be done via direct web randomization. Authorized study center personnel will randomize the patient via a password protected internet website. The randomization system will then determine the treatment arm and provide the subject number to be used for the patient. The site monitor/clinical research associate (CRA) will be informed immediately in the event that the web randomization is not successful. Back-up randomization opaque envelopes (and related procedures) will also be prepared and provided to the site in case of internet failure.

Study arm allocation will not be blinded.

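### The plan sends interim by-arm safety details and any significant efficacy differences to the Trial Steering Committee, when the DSMB's recommendation alone would do

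*Protocol article*

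**What the plan says.** All of the relevant text is in the protocol article, under Safety considerations, Randomization and Study design.

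- **Timing and content.** There is one interim analysis, "including both efficacy and safety endpoints will be performed after the first 50 subjects have completed 12 weeks of the study".
- **First recipient.** "The trial statistician will provide details of safety outcomes and any significant differences in efficacy according to treatment arm to the DSMB". The board is described as "comprising two independent physicians and a statistician".
- **Second recipient.** The next sentence reads "These will be highlighted to the Trial Steering Committee along with the" DSMB's recommendations for action.
- **Stopping route.** If there is a significant safety concern, "the DSMB may recommend to the PI that the trial should be stopped". No efficacy stopping rule is stated.
- **Blinding.** "Study arm allocation will not be blinded", and Study design describes the trial as open-label and non-inferiority.

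The article mentions the Trial Steering Committee only here and does not give its membership. It describes no closed session and no limit on who may see by-arm interim results.

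**The concern.** In an open-label trial each patient's assignment is known, but the accumulating comparison between arms is not. Keeping that comparison confidential is one of the few protections left against patients being handled differently by arm. The sentence on the steering committee gives it up.

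The plan leaves room for such handling. Withdrawal criteria let the investigator take a patient off study treatment on a best-interest or safety judgement. Discharge is left to the treating team, and length of stay is a secondary endpoint. Antibiotic escalation, unplanned drainage and readmission are endpoints that depend on clinical decisions.

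The analysis sets would not remove the effect. Both count a patient who leaves the allocated treatment after the first dose: the ITT set by randomized arm, and the per-protocol set by first dose received, provided the primary endpoint was measured. In a non-inferiority trial, moves between treatments prompted by interim news can pull the arms together.

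**Working it through.** **1. What is disclosed.** Read the two sentences in order. The first names two items: details of safety outcomes, and any significant efficacy differences, according to treatment arm. The second opens with a plural pronoun whose only natural antecedent is those two items. It sends them to the committee together with the recommendations. The findings therefore travel in addition to the advice. This is a positive instruction to disclose. A charter that restricted disclosure would contradict it.

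**2. Whether the plan needs the disclosure.** The only stated stopping route is a safety concern, recommended by the DSMB to the PI. No efficacy rule calls for committee judgement on by-arm data.

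**3. How wide the efficacy channel is.** The article names no interim test. Assume 25 per arm (50 patients at 1:1) and a two-sided Fisher exact test at 0.05. Failures out of 25 in each arm:

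| Failures | p |
|---|---|
| 0 v 5 | 0.0502 |
| 0 v 6 | 0.022 |
| 1 v 6 | 0.098 |
| 1 v 7 | 0.049 |

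The smallest significant gap is 6/25 = 24 percentage points, twice the 12-point margin. The chance of such a result comes from summing binomial probabilities over all significant tables:

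| True cure, control v oral | Chance that a significant difference is forwarded |
|---|---|
| 95% v 95% | 0.08% |
| 95% v 90% | 1.3% |
| 95% v 83% | 11% |

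The 95% is the control rate under Determination of sample size. The oral-arm rates are assumptions. In most cases the committee would learn only that no very large gap was seen.

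**4. How wide the safety channel is.** No significance filter applies to safety. The safety endpoints listed under Study endpoints include antibiotic escalation for worsening infection. Safety details by arm therefore carry some information about efficacy.

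**5. How many patients come after the look.** The plan's total reproduces from its 64 per arm: 64/(1 − 0.15) = 75.3, so 76 per arm and 152 in all. Assuming uniform accrual over the planned two years:

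- Accrual rate: 152/24 = 6.33 per month.
- 50 enrolled at 50/6.33 = 7.9 months; 12 weeks of follow-up adds 2.8 months, giving 10.7 months.
- Enrolled by then: 10.7 × 6.33 ≈ 68. Still to enrol: 152 − 68 = 84 (84/152 = 55%).
- Outcomes not yet in the interim data: 152 − 50 = 102 (67%).

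Both counts are upper bounds. Each month of lag for cleaning, analysis and meeting lowers the 84 by about 6. If 15% drop out before week 12, then 50/0.85 = 58.8 must be enrolled to give 50 completers. The look then moves to 58.8/6.33 + 2.8 = 12.1 months, with about 76 enrolled and about 76 (50%) to come. The 102 likewise includes patients expected to drop out.

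**The case against.** The strongest reply is that little would be released, and that it might reach nobody who treats patients. Much of this stands.

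- **Full results.** A reader might infer that cure rates by arm go to the committee. The text forwards only significant efficacy differences, which step 3 shows to be unlikely. It does not support the broader reading for efficacy, though it does for safety details.
- **Who passes it on, and to whom.** A reader might infer that the DSMB passes the data to the people running the trial. The sentence is passive and names no sender. The article does not say that committee members enrol or manage patients; that is an inference from what such committees usually do.
- **Enrolment by arm.** A reader might add enrolment to the behaviours that could shift by arm. It precedes allocation, which is by central web randomization in permuted blocks of undisclosed length. Interim news could change who is recruited or how fast, but not by arm.
- **The primary endpoint.** It rests on a CRP threshold, recorded temperature and measured abscess diameter, and continuation of antibiotics after week 4 follows set criteria. Patients withdrawn from the intervention are to stay in follow-up. Drop-outs are imputed as cured only if CRP and temperature conditions hold as well as the phone report. Conduct and the secondary endpoints are therefore more exposed than the primary endpoint.
- **Open label already.** Discretion over withdrawal, discharge and escalation exists anyway. Even so, knowing individual assignments is not the same as knowing the pooled comparison.

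None of this supplies a reason for the committee to receive the by-arm findings.

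**Conclusion.** The point holds in a limited form. The article directs that interim safety details and any significant efficacy differences by arm go to the Trial Steering Committee alongside the recommendation, and nothing else in it restricts this. That is an avoidable risk to trial conduct, worth correcting because the correction is cheap and a disclosure cannot be undone.

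The wording is clear; the consequence is less certain. It depends on committee members being involved in running the trial, which the article does not say. For efficacy, disclosure would need a gap of about 24 points under the assumed interim test. For safety, it would happen whatever the result. At most about 84 of 152 patients would be enrolled afterwards, and fewer with reporting lag or attrition.

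A reader might also infer that the plan allows an early claim of non-inferiority at this look. The article states no such claim, so that is a separate matter. Sample size is not affected.

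**What to change.** Replace the sentence on the steering committee with wording such as: *Comparative results by arm remain confidential to the DSMB and the statistician preparing its report; the Trial Steering Committee receives only the DSMB's recommendation.* Repeat the rule in the DSMB charter, if there is one, so that the two agree.

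The cost is one sentence. Sample size, endpoints and patient management do not change. The downside is that the committee has less detail when it acts on a recommendation.
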